# A Digital Platform (Telepalliation) for Patients in Palliative Care and Their Relatives: Protocol for a Multimethod Randomized Controlled Trial

**DOI:** 10.2196/49946

**Published:** 2024-04-02

**Keywords:** palliative care, digital health, quality of life, telehealth, interdisciplinary research, randomized controlled trial

## Abstract

**Background:**

The World Health Organization defines end-of-life palliative care as “prevention and relief of suffering, by means of early identification and impeccable assessment and treatment of pain and other problems, physical, psychosocial and spiritual.” Over 20 million people worldwide are in need of palliative care. In Denmark, palliative care is given at a general and a specialist level. The general level comprises health care professionals (HCPs) who do not perform palliative care full-time. The specialist level comprises specialized palliative care (SPC), where HCPs perform palliative care full-time. In total, 20%-30% of patients who need palliative care are referred to SPC. Challenges with SPC include a short time span from referral to end of life, patients who are very ill and may therefore find it hard to travel to an outpatient clinic, and the SPC unit having a relatively small staff. The need for SPC is expected to rise, as the number of patients dying from terminal diseases is increasing. Telehealth has been successfully implemented in different home care settings, including palliative care.

**Objective:**

The aim of the study is to present the research design of the clinical testing of a telepalliation program by the use of a digital platform for patients in palliative care and their relatives.

**Methods:**

The telepalliation program will be conducted as a multimethod randomized controlled trial. The intervention group will follow the telepalliation program, while the control group will follow the traditional standard of care program for palliative care. The primary outcome of the study is increased quality of life. Secondary outcomes include enhanced sense of security; reduced experience of pain; satisfactory experiences of patients and relatives with the TelePal platform and degree of satisfaction in being a part of the program; experiences with the use of the TelePal platform on the part of HCPs and the professionals’ experiences of being a part of the program; the use of a cross-sector communication platform and the telepalliation program by patients, relatives, and HCPs; and the projected lower cost of health care services. These outcomes will be assessed using questionnaires, data generated by digital technologies, and semistructured interviews.

**Results:**

The collection of data began in May 2021 and will be completed in August 2024. The results of the study will be published in peer-reviewed journals and presented at international conferences. Results from the telepalliation program are expected to be published by fall 2024.

**Conclusions:**

The expected outcomes of the study are increased quality of life and increased sense of security. We also expect that the study will have a clinical impact on future telepalliation for those patients who are referred to a palliative team.

**Trial Registration:**

ClinicalTrials.gov NCT04995848; https://clinicaltrials.gov/study/NCT04995848

**International Registered Report Identifier (IRRID):**

DERR1-10.2196/49946

## Introduction

The World Health Organization defines end-of-life palliative care as “prevention and relief of suffering, by means of early identification and impeccable assessment and treatment of pain and other problems, physical, psychosocial and spiritual” [1]. The aim of palliative care is to provide relief from pain and other distressing symptoms offered by health care professionals (HCPs) at a general or specialist level, with a focus on addressing the needs of patients and their families [1,2]. More than 20 million people worldwide are estimated to be in need of end-of-life palliative care, equivalent to 377 adults in a population of 100,000, the majority of these being adults aged 60 years and older [2].

In Denmark, as in most other Western European countries, palliative care is provided at 2 different levels, a general and a specialist. The general level comprises HCPs, such as general practitioners (GPs) and primary care nurses, who do not perform palliative care on a full-time basis. The specialist level comprises specialized palliative care (SPC), where HCPs perform palliative care on a full-time basis at a specialist level [3]. It is expected that the basic level palliative care can address around 70%-80% of the patients in need of palliative care. The remaining 20%-30% of patients, having more complex problems, need SPC. SPC consists of specialized palliative care teams (SPCTs) placed at large hospitals serving a wider geographical area with home visits and cross-sector communication with patients, relatives, and other HCPs capable of caring for the patients.

Among patients receiving SPC, more than 90% are diagnosed with cancer [4], with the remaining cases divided among patients diagnosed with terminal cardiac insufficiency, terminal chronic obstructive pulmonary disease, and terminal neurological disorders [2,4].

There are several challenges associated with SPC, such as the very short time span from referral to the end of the patient’s life [4] and the fact that patients are very ill and may therefore find it hard to travel to an outpatient clinic and that SPC unit often has a relatively small staff [2,5-7]. The need for SPC is expected to rise in the future, as the number of patients dying from life-threatening diseases, including cancer, is increasing [5,8]. As an increasing number of these patients prefer to be cared for at home, the demand for SPC is expected to increase [5,8].

The use of telehealth has been introduced in different settings and at different levels of home care and has also been used with success in palliative care [8,9]. Demand for telehealth solutions in palliative care has also increased due to the COVID-19 pandemic [10,11]. The use of information and communication technologies within palliative care can be defined as “telepalliation.”

The overall purpose of the telepalliation study is to test, implement, analyze, and evaluate a telepalliation program for patients receiving palliative care. To accomplish this goal, we combine clinical, psychosocial, interorganizational, and health economic approaches. The telepalliation study will be implemented and evaluated in a randomized controlled trial (RCT). The aim of this paper is to describe the research design of the telepalliation study, the data collection methods used, and the outcome measures.

## Methods

### Research Design

The telepalliation program will be conducted as a multimethod RCT using qualitative and quantitative data collection techniques [12,13]. The intervention group will take part in the telepalliation program, while the control group will follow a traditional palliation program at Southwest Jutland Hospital, Esbjerg, Denmark. Enrollment of patients began in May 2021, and the RCT will end in August 2024. The study will be reported following the SQUIRE (Standards for Quality Improvement Reporting Excellence) guidelines [14].

The purpose of the telepalliation study is to test, implement, and evaluate a telepalliation program for patients receiving SPC at the Hospital of Southwest Jutland, Esbjerg, Denmark. To accomplish this goal, we combine clinical, psychosocial, interorganizational, and health economic approaches. This will be done by collecting data on symptom scores over time, patients scoring their feeling of security over time, and interviews with patients, their families, HCPs of the specialist team, and primary HCPs. Interviews will focus on the use of the TelePal platform but also on the interorganizational perspective of the communication between primary and secondary health systems. Evaluation of overall economic implications will be done separately at the end of the study. The telepalliation study will be implemented and evaluated in an RCT.

### The TelePal Platform

The telepalliation program and platform have been developed through a participatory design process [15], involving patients who have received SPC and their relatives, HCPs working in palliative care, district nurses, GPs, and an interdisciplinary research team.

The study uses a TelePal platform, a communication platform that is shared among the patient, his or her relatives, and related HCPs. The platform can be used to communicate between patients, their families, and HCPs in primary and secondary health care. The patients must give their written consent as to whom they want to share their data. All information will be available and presented in the same way to all participating parties. The HCPs and researchers have extra tools with which to administer care, gain an overview of the patient’s condition, and monitor multiple patients at the same time. The digital platform is not an electronic patient record but a platform for coordination and communication across sectors between patients, relatives, and HCPs.

All the measured values are stored on a secure database at Aalborg University (AAU). The TelePal web portal (Figure 1) is a web-based platform that encompasses multiple features that have been selected and developed through user-driven innovation [16]. Facilities and entered data (symptom scores, etc) of the specific patient are available to the persons, to whom the patient allows access to the platform. The features are described in Textbox 1.

**Figure 1 figure1:**
[figure not shown]
Overview of the TelePal platform.

Features of the TelePal web portal.
**My page/front page (*Min side* in Danish); used to give the patient an overall overview of the different features)**
New messagesVideo consultations (the patient can have video conversations with the palliative team, district nurses, and GPs via TelePal. However, only the HCPs can book meetings with patients and their relatives)Questionnaires for patients to fill out
**My treatment (*Mit forløb* in Danish)**
Dialogue function (here, the patients can send and reply to messages to the palliative team and the district nurses; if the patient so desires, an SMS function can be used to inform the patient about new messages on TelePal)Calendar (gives the patient the opportunity to register coming appointments with the palliative team or any other activity for an overview)Joint notes (notes related to the patient’s treatment are written here by either the palliative team, the home nurse, or GPs)Own notes (these are the patient’s own notes, thoughts, questions, and reflections, if they want to use this function)
**My status (this site provides the patient with an overview of the results from all the questionnaires they have filled out)**
The data from the questionnaires are visible to the patient’s relatives and HCPs, if the patient has allowed them to see and follow their data on TelePal.Patients may decide themselves whether they want to allow up to 2 relatives to have access to their TelePal platform. It is also the patient who defines what relatives should have access.

### Data and Network Security

The TelePal platform is web-based. It is possible to access the platform from any internet-enabled device, for example, a PC or Mac computer or a tablet, via any modern browser. The most optimal experience and resolution will appear when using an iPad or tablet. All communication and data are secured based with SSL and a 2-factor log-in. The portal will be kept at AAU on servers provided by AAU IT services.

### Eligibility Criteria

All participants will be recruited by 2 project nurses at the palliative team at Southwest Jutland Hospital, Esbjerg, Denmark. Recruitment will take place by personal contact and by a recruitment letter. Enrollment will proceed if the participant fits the inclusion and exclusion criteria. Inclusion criteria for participants are that they must be patients under SPC at the Hospital of Southwest Jutland; be aged 18 years or older; live in Esbjerg, Varde, Billund, Fanø, or Vejen municipalities; have cancer, heart failure, chronic obstructive pulmonary disease, or motor neuron disease; and have basic computer skills or have a relative who is able to help them. The exclusion criteria are delirium at enrollment based on the Confusion Assessment Method score; an active psychiatric history other than depression or anxiety related to the main diagnosis, which refers to the reason for palliative care; and a lack of cooperation. Enrollment will take place at the patient’s home, where a doctor and a nurse from the palliative team will take the inclusion and exclusion criteria into consideration. Patients who are moribund are not assessed for participation in the study. The patient will be given complete information about the project, and the palliative team will obtain informed consent. The project nurse will then proceed to explain to the patient how to use the equipment and the TelePal portal. If the patient meets the inclusion criteria and agrees to be included, randomization to either the intervention group or standard care will be made.

### Details on the RCT

The randomization is performed randomly by a digital tool. The randomization was designed as a block with equal numbers for the intervention and control groups. Only 1 person was blinded. The intervention group participated in the telepalliation program, and the control group received standard SPC [1,3] that was individualized for each patient.

### Sample Size

The sample size of the telepalliation study was determined to be 91 patients in both the intervention and the control groups when calculating values based on Ramsenthaler et al [17]. This was done using a 95% CI, an 80% power, an SD of 20.5, a mean quality-of-life score of 59.5 determined by the European Organisation for Research and Treatment of Cancer, and a mean quality-of-life score of 68.43 determined by the European Organisation for Research and Treatment of Cancer when operating with a 15% change in quality of life (QoL).

### Theoretical Framework

The theoretical framework is applied as lenses in qualitative analysis.

#### Psychosocial

In recent years, increasing attention has been paid to the importance of psychosocial factors in palliative care and how these factors can play a crucial role for good end-of-life care in terms of alleviating pain and other distressing symptoms [18]. The World Health Organization [1,19] stated that control of pain, psychological disorders like anxiety and depression, and social and spiritual problems is paramount in palliative care.

Research shows that an intervention focused on the assessment of pain and psychosocial symptoms, establishment of goals of care, assistance with decision-making regarding treatment, and individualized coordination of care can all significantly improve patient QoL. Patients reported less depression and physical symptom burden and lived an average of 2.7 months longer than the usual care group, despite receiving less aggressive care [20].

#### Interorganizational Theory

Collaboration across sectors in the telepalliation program will be studied through the lenses of interorganizational theory by Alter and Hage [21]. The network approach facilitates an exploration of the interplay, communication, collaboration, and dynamics between the HCPs, for example, palliative team, district nurses, and GPs across borders and sectors when developing and implementing the telepalliation program. Alter and Hage [21] define a network as follows: “Networks constitute the basic social form that permits inter-organizational interactions of exchange, converted action, and joint production. Networks are unbounded or bounded clusters of organizations that, by definition, are non-hierarchical collectives of legally separate units.”

### Ethical Considerations

This study was approved by the ethical committee in Northern Jutland (N-202000094) and registered at ClinicalTrials.gov (NCT04995848). This study will be conducted according to the Declaration of Helsinki. Patients in palliative care and their relatives are a vulnerable group and will be informed thoroughly about the purpose of the study. Accordingly, it is specified that the patient can withdraw their consent at any given time in the study without having any consequences for their treatment. Individuals will be considered as participants in the trial, whereas their relatives will not be considered as participants. However, they are invited to voluntarily participate in the use of the digital platform TelePal. To clarify and ensure that all relatives are fully informed about the study and feel safe about their participation, a written letter of information was sent to all relatives. Patients are enrolled in the study for a maximum of 6 months or until (1) they stop being followed by the palliative team due to lack of symptoms or (2) they are diagnosed with delirium based upon the Confusion Assessment Method score [22,23]. Patients who develop cognitive impairment will be dismissed from the study, and patients who develop delirium will also be dismissed, and data collection will end immediately.

**Primary**				
	Quality of life	Once weekly	✓	✓
**Secondary**				
	Changes in medicine	Weekly for 6 months	✓	✓
	Pain assessment	Weekly	✓	✓
	Feeling of security	Twice a week	✓	✓
	Patients’ experiences	Interviews will be conducted after 4 weeks	✓	
	Relatives’ experiences	Interviews will be conducted after 4 weeks and after 3 months	✓	
	Health care professionals’ experiences	Interviews will be conducted at 6 and 12 months		
	Use of the TelePal platform and telepalliation program	Analysis at the end of the project	✓	✓
	Cost of health care services	Week 1 and week 4, and analysis at the end of the project	✓	✓
	Quality of life associated with cost of health care services	Week 1 and week 4, and analysis at the end of the project	✓	✓

### Outcome Measures

#### Overview

Primary and secondary outcome measures will be collected as shown in Table 1. The data collection process is described in the following sections.

#### Quality of Life

The EORTC QLQ-C15-PAL (European Organisation for Research and Treatment of Cancer Quality of Life Questionnaire Core 15 Palliative Care) [24] questionnaire will be used to measure QoL as the primary outcome. The EORTC QLQ-C15-PAL was developed by the European Organization for Research and Treatment of Cancer to measure the QoL for patients in palliative care. It is a briefer version of the EORTC QLQ-C30-PAL I, as this patient group is often not able to complete extensive self-report measures. It consists of 15 items, of which, all but one (global QoL) is self-rated on a 4-point Likert scale (1=not at all to 4=very much), whereas global QoL is rated on a 7-point Likert scale (1=very poor to 7=excellent). In this study, we did not use the global QoL item. Items are used to calculate scores on 2 multi-item functional scales (emotional and physical), 2 multi-item symptom scales (fatigue and pain), and finally, they contribute to 5 single-item symptom scales (nausea or vomiting, lack of appetite, shortness of breath, constipation, and sleeping difficulties). The EORTC QLQ-C15-PAL is considered to have good content validity [24], and a recent study comparing measures of QoL in palliative care found acceptable internal consistency and test-retest reliability as well as sensitivity of the EORTC QLQ-C15-PAL, while overall results indicated that no other QoL measure is superior to use in this patient group [25].

In addition, the EQ-5D health questionnaire was used to determine QALY to support our analysis on the cost of health care services, as no other QoL measure is validated for this purpose. Hence, we incorporated EQ-5D, the EQ Visual Analog Scale from the EQ-5D, which records the patient’s self-rated health on a vertical visual analog scale using the end points, the best health you can imagine and the worst health you can imagine. This scale can be used as a quantitative measure of health outcomes that reflect the patient’s own judgment [26]. Studies have shown good construct validity and responsiveness in palliative care [27], and a recent systematic review finds that the EQ-5D has excellent psychometric properties across a broad range of populations [28].

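### The primary outcome is one quality-of-life construct, but the nine scores listed include no overall score and no designated primary, and the sample-size score is linked to none of them

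*Protocol article*

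**What the plan says.** The abstract treats the primary outcome as one construct: "The primary outcome of the study is increased quality of life". Table 1 lists it simply as quality of life, collected once a week in both groups. Under Outcome Measures, Quality of Life, the EORTC QLQ-C15-PAL "questionnaire will be used to measure QoL as the primary outcome".

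That section identifies one item of the instrument as the global quality-of-life rating and then says: "In this study, we did not use the global QoL item". It goes on to describe what is scored: "Items are used to calculate scores on 2 multi-item functional scales (emotional and physical), 2 multi-item symptom scales (fatigue and pain"), followed by five single-item symptom scales (nausea or vomiting, appetite, breathlessness, constipation, sleep). It describes no total or summary score.

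The Sample Size section uses one score, "a mean quality-of-life score of 59.5 determined by the European Organisation for Research and Treatment of Cancer", with SD 20.5 and a target mean of 68.43 after a 15% change. It arrives at 91 patients per group. The Statistical Analysis section compares the groups on their outcomes by a two-way repeated-measures ANOVA and does not say which score decides the trial.

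**The concern.** The parts of the article do not fit together. It names one construct, removes the only item that rates that construct as a whole, lists nine component scores, and sizes the trial on one overall-sounding score that is not identifiable among the nine.

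Two things are at stake. First, the power statement has no known owner: a mean, SD and target difference are given, but not for any score the article lists. Second, the conclusion that quality of life increased is not tied to a particular result. If the deciding scale is chosen after the group results are known, a favourable finding on one of nine scales could be presented as the primary result, and a reader could not tell whether the choice came first.

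**Working it through.** **Step 1. Count the scores.** From the Quality of Life section: 2 functional + 2 multi-item symptom + 5 single-item symptom = 9. The global item is excluded.

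**Step 2. Look for the sample-size score among them.** The Sample Size section gives one mean (59.5), one SD (20.5) and one target. The target is 59.5 × 1.15 = 68.425, stated as 68.43, so the difference is 68.43 − 59.5 = 8.93 points and the standardised difference is 8.93 / 20.5 = 0.436. None of the nine scores is called a quality-of-life score, and no mean or SD is given for any of them. The EQ Visual Analog Scale does not fill the gap: the article assigns it to the QALY and cost work, it is collected only in weeks 1 and 4, and Table 1 places that use among the secondary outcomes.

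**Step 3. Reproduce the stated figure.** Inputs: two-sided 5% (read from the stated 95% CI), 80% power, 1:1 allocation.

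n per arm = 2 × [(1.960 + 0.842) × 20.5 / 8.93]² = 82.7, so 83 (84 with the t distribution).

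The stated 91 is not reproduced. It would follow from an inflation of about 10% (82.7 × 1.10 = 91.0), but none is stated. At 91 per arm the stated inputs give 83% power by the t test (83.2%; normal approximation 83.6%). So 91 is more than enough for the stated inputs. The difficulty is that those inputs are not attached to a listed score.

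**Step 4. Chance of a false claim of benefit if any one of nine scales could carry it.** Assume no true effect, each scale tested at two-sided 5%, and only results favouring the intervention counted (2.5% per scale).

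- Independent scales: 1 − 0.975⁹ = 0.204.
- Common correlation ρ: 1 − ∫ φ(u) Φ[(1.960 − √ρ·u)/√(1−ρ)]⁹ du, by numerical integration.

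| Assumed correlation | Chance of at least one false benefit |
|---|---|
| 0 | 20.4% |
| 0.4 | 15.0% |
| 0.6 | 11.8% |
| One scale only | 2.5% |

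**Step 5. How far power depends on which score is chosen.** Two-sample t test, 91 per arm, two-sided 5%, difference held at 8.93 points. Only the first SD is in the article; the other two are assumed.

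| SD | Power at 91 per arm |
|---|---|
| 20.5 (stated) | 83% |
| 25 (assumed) | 67% |
| 30 (assumed) | 51% |

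These figures are for a simple two-group comparison, not the repeated-measures analysis. They illustrate sensitivity and do not forecast the trial's power.

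**The case against.** The best defence is that an article condenses. A statistical analysis plan may name the deciding scale, define a composite or set a multiplicity rule, and its absence here is not a fault. That is right as far as it goes: the article states no rule that success on any one scale suffices, and it does not say that nine unadjusted tests will support the headline claim. A reader might infer an uncontrolled error rate, but the article shows only an unspecified one, so the percentages in Step 4 are conditional. The defence does not remove the mismatch, because the article itself fixes the construct, the scores and the sample-size basis. Even if a later plan picks a scale, 59.5 and 20.5 would still have to be shown to apply to it.

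Four stronger readings are tempting and should be resisted.

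- **That the trial is powered for something it does not measure.** The Sample Size section does not say which EORTC score its inputs come from, and the cited source is not at hand. They could belong to a global item, a subscale or a composite. What is established is the missing link.
- **That the primary outcome has no score at all.** Nine scores exist; what is missing is an overall score or a designated one.
- **That the false-positive risk is 37%.** The figure 1 − 0.95⁹ = 0.370 counts chance findings in both directions, including apparent worsening. The claim at issue is of improvement.
- **That true power is about 55% under a Bonferroni split.** This applies the 8.93-point difference and SD 20.5 to all nine scales, although the article links them to none, under a correction it does not propose.

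Nor does the point require a single time point. The weekly repeated-measures comparison is not shown to be wrong.

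**Conclusion.** The point stands as an internal conflict. The article rests its primary outcome and its sample size on one quality-of-life score, excludes the only item rating quality of life overall, and lists nine scores without describing a summary or designating a primary. The stated 80% power therefore cannot be attached to any listed score.

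The potential size is a false-benefit risk of about 12% to 20% instead of 2.5%. This assumes nine tests at two-sided 5%, any one of which could support the claim, and equal correlations between 0 and 0.6. The correlations are assumed, and the any-one rule is a possibility the article leaves open, not one it adopts. The count of nine and the lack of a stated link come directly from the text. It must be settled before the comparative analysis, because a primary score chosen after the group results are known would not be credible.

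**What to change.** Issue a dated amendment before the comparative analysis that does the following.

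1. Names one collected scale, or one pre-defined composite of the retained items with its scoring and direction, as the primary endpoint.
2. States the specific contrast from the weekly data that decides the trial. This can remain a repeated-measures contrast.
3. Makes the remaining scales secondary, or applies Holm to any that may support a quality-of-life claim.
4. Restates the power at 91 per arm with the SD and target difference of the chosen score. The 59.5 and 20.5 justification should stay only if it is shown to apply to that score.
5. Declares who has already seen outcome data by arm. The article says only one person was blinded, gives health care professionals and researchers tools to follow patients on the platform, and places the analysis in spring 2024, so complete blindness cannot be presumed.

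The cost is drafting time and matching wording in the analysis plan, with no new patients or measurements. The downside is that the restated power may be lower than the article's 80%.
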